#### Mediators

Four variables will be assessed as potential mediators: (a) Parental-reported exposure protection (PREP) behaviors are measured with self-report items used in our previous research and reflected in a recent meta-analysis. We operationalize PREP behavior in two measures: (1) families’ current home smoking policy (0 = no restrictions to 4 = total indoor ban); and (2) the sum of 10 PREP behaviors (e.g., move child away from others’ smoking). (b) Support for TSE protection and smoking cessation will be measured using a modified short form of the Partner Interaction Questionnaire. The modified measure, used in our previous multilevel trial [20], assesses perceived intervention staff support to participants for promoting TSE reduction and cessation (α = .91). (c) Self efficacy of smoking behavior change will be measured using the Smoking Cessation Self-Efficacy Scale (α = .90) and a parallel form (α = .90) we developed [20] to assess self-efficacy in reducing child TSE. (d) Urge management and coping will be assessed using the Urge Management Coping Skills measure [20] based on cognitive and behavioral coping strategies identified by O’Connell (α = .87).

#### Covariates and moderators

Four variables will be assessed as potential control variables and moderators of intervention effects: (a) Nicotine dependence will be measured with the reliable and validated Fagerström Test for Cigarette Dependence [43]. (b) Depressive symptoms will be measured with the Center for Epidemiological Studies Depression Scale, which are validated, reliable and useful in smoking studies [44]. (c) Weight concerns will be measured using a 6-item validated scale that measures general and smoking-specific weight concerns [45]. (d) Other smokers in mothers’ homes will be assessed using a standard, content valid item. Additional demographic and smoking history variables will be measured and assessed for possible association with outcomes.

#### Process measures and treatment fidelity

Intervention processes will be assessed in both conditions with multiple methods and at each time point and intervention level: WIC clinic AAR implementation (e.g., participant reports of advice received; WIC counselor report of attitudes and practices), telephone counseling (e.g., counselor reports of attendance, duration, participant engagement), NRT utilization (e.g., participant-reported compliance), and mobile app usage (e.g., pushed data reflecting frequency of launching and using specific features).

### Analytic plan

The predictor is intervention group (AAR + MBI vs. AAR + Control) and the two endpoints include child exposure (continuous primary outcome) and parent cessation (dichotomous secondary outcome). Primary analyses will use an intention-to-treat approach and missing data will be addressed using multiple imputation. In sensitivity analyses, we will perform complete case analyses and investigate the impact of data that is potentially missing not at random. We will compare child cotinine change scores between intervention arms using multilevel random-effects linear regressions in which we include randomization arm as a fixed effect and WIC clinic as a random intercept to account for potential clustering within clinic. Potential confounders (e.g., nicotine dependence) will be added as covariates as necessary. We will use multiple logistic regressions with random intercepts for clinic to compare bioverified self-reported quit status (yes/no) between randomization arms at 3 and 12 months. To investigate mediation pathways, we will use a structural equation approach with change in cotinine levels and parent quit status as the outcomes. We will ensure that the intervention is associated with the potential mediators (e.g., self-efficacy) and that the mediators are associated with the outcomes. We will also use cluster-adjusted bootstrap standard errors for assessment of the mediated effect in which the variables are measured in a temporal ordering consistent with a causal pathway. For moderation analyses, we will use random-effects multiple regression modeling the change in cotinine levels and parent quit status, using confounding variables as necessary.

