#### Power analysis

We chose our sample size so that we would have at least 85% power to detect between-group differences in the primary outcomes (3- and 12-month child cotinine). Using an estimate of 20% 1-year follow-up attrition based on the KiSS trial, we expect to have 298 participants at 12 months (372*80% retention = 298, or 149 per group). With 149 participants per group, we will have 85.7% power to detect an effect of 0.23 in the log cotinine change scores between randomization arms.

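### The primary cotinine model does not prespecify adjustment for baseline cotinine or carry over the log scale on which the trial was powered

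*Protocol article*

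**What the plan says.** All references are to the protocol article.

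- **Analytic plan, outcome.** "We will compare child cotinine change scores between intervention arms using multilevel random-effects linear regressions". No transformation is named here, and the mediation and moderation models are also described in terms of change in cotinine.
- **Analytic plan, model terms.** "we include randomization arm as a fixed effect and WIC clinic as a random intercept to account for potential clustering within clinic". Baseline cotinine is not among the terms.
- **Analytic plan, other covariates.** "Potential confounders (e.g., nicotine dependence) will be added as covariates as necessary".
- **Power analysis.** The sample size rests on "85.7% power to detect an effect of 0.23 in the log cotinine change scores between randomization arms", with "372*80% retention = 298, or 149 per group". Cotinine at both 3 and 12 months is called a primary outcome. The SD, alpha, sidedness, log base and baseline-to-follow-up correlation are not given.
- **Aims and hypotheses.** Hypothesis 1 is worded as a greater reduction in child urine cotinine from baseline to each follow-up.
- **Procedures.** Randomization is stratified by clinic site and by whether other smokers live in the home. Only clinic appears in the stated model.

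**The concern.** Two features of the stated model are weaker than they need to be.

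**Baseline cotinine.** A change score is a regression on baseline with the slope fixed at 1. If the true slope is below 1, as it is when the two SDs are equal and the correlation is below 1, the change score over-corrects any chance baseline difference between the arms and carries extra variance. Estimating the slope removes that variance. Since the change score already requires a baseline value, the gain needs no further measurement.

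**Scale.** The model sentence refers to cotinine change and the power sentence to log cotinine change. The former, read literally, targets a difference in mean change in concentration; the latter, once exponentiated, targets a ratio of geometric means. The primary model should state the powered quantity.

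At stake is precision on the trial's main comparison and clarity about what the arm coefficient means.

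**Working it through.** **Inputs from the article:** 372 randomized, 20% attrition, 149 per group, effect 0.23 in log change, power 85.7%.

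**Assumptions:** alpha 0.05 two-sided; 0.23 is a raw difference on the log scale; equal baseline and follow-up SDs on the log scale; correlation rho between 0.3 and 0.9; clinic clustering ignored.

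**1. The plan's own figures.** 372 × 0.80 = 297.6, so 298, or 149 per group, reproduces. The 85.7% can be neither confirmed nor refuted without an SD. If 0.23 were a standardized difference, power would be 51.0% (two-sided 0.05), so that reading does not fit. Taken as a raw log difference, the SD that yields 85.7% is

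SD = 0.23 × √(149/2) / (1.960 + 1.067) = 1.985 / 3.027 = 0.656,

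a standardized difference of 0.23/0.656 = 0.35. A noncentral t calculation gives 0.654.

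**2. Variance with and without baseline adjustment.** Write s0 and s1 for the baseline and follow-up SDs.

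- Change score: s0² + s1² − 2·rho·s0·s1
- Adjusted for baseline: s1²(1 − rho²)
- Difference: (s0 − rho·s1)², which is never negative

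So, apart from one degree of freedom, adjustment cannot lose precision on the same scale. With s0 = s1 the variance ratio is (1 − rho²)/(2(1 − rho)) = (1 + rho)/2.

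**3. Power at 149 per group,** as Φ(3.027/√ratio − 1.960):

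| rho | Variance ratio | Power, log model with baseline | n per arm for 85.7% |
|---|---|---|---|
| 0.3 | 0.65 | 96.4% | 97 |
| 0.5 | 0.75 | 93.8% | 112 |
| 0.7 | 0.85 | 90.7% | 127 |
| 0.9 | 0.95 | 87.4% | 142 |

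The comparator is 85.7% with 149 per arm.

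**4. Sensitivity.**

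- *Unequal SDs.* With k = s1/s0, the ratio is k²(1 − rho²)/(1 + k² − 2·rho·k). At rho 0.3, 0.5 and 0.7 it is 0.50, 0.57 and 0.63 for k = 0.8, and 0.76, 0.87 and 0.97 for k = 1.2. The size of the gain varies but its direction does not.
- *One-sided alpha 0.05.* The back-solved SD is 0.732. At rho 0.5, power is Φ(2.712/√0.75 − 1.645) = Φ(1.487), about 93%, close to the two-sided result.
- *Simulation* (3,000 trials per setting, lognormal data). At rho 0.3, 0.5 and 0.7, log change gives 87%, 85% and 86%, and the log model with baseline gives 96%, 94% and 91%. This agrees with the formulas.

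**5. Same target.** Log change equals log follow-up minus log baseline. Once log baseline is a covariate, using log change or log follow-up as the outcome gives the same arm coefficient. Hypothesis 1's wording about reductions is therefore preserved.

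**The case against.** The best defence is that nothing here is an error. Change runs consistently through Hypothesis 1, the mediation and moderation models and the power statement. Under randomization, regression to the mean acts equally on both arms in expectation, so the between-arm difference in change is unbiased. That stands: baseline adjustment improves precision and does not rescue an invalid method. Only the log part of the fix matches the powered quantity; the covariate is an addition.

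Several stronger readings are tempting but are not supported:

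- *A raw-scale analysis is planned.* The Analytic plan omits the log; it does not say untransformed, and the Power analysis suggests log change was intended. Simulated power for raw change (73%, 68% and 58% at rho 0.3, 0.5 and 0.7, natural log) describes an analysis nobody has stated. The decline also partly reflects holding the change SD at 0.656, which pushes the implied log-cotinine SD from 0.55 to 0.85.
- *The model is unadjusted, or its covariates will be picked after seeing outcomes.* Covariates are explicitly allowed, and candidate control variables are listed under Covariates and moderators. The rule for including them is ordinary analysis-plan content. What can be said is that the stated primary model does not commit to baseline cotinine.
- *Adjustment first needs a urine sample taken before allocation.* Under Procedures, urine is collected at the orientation home visit, after randomization. That affects change scores and baseline adjustment alike, and is a separate point.

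It is also fair that the size of the gain cannot be derived from the article, and that it falls below 2 percentage points at rho 0.9.

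**Conclusion.** The point holds as a matter of efficiency and clarity. The stated primary model leaves out a covariate that the trial must have anyway, and does not name the scale used for the sample size. On the log scale, and under the assumptions listed in the calculation, prespecified adjustment for baseline would add about 2 points of power (rho 0.9) to 11 points (rho 0.3) to the stated 85.7%. The SD, alpha, correlation and equality of SDs are all assumed. The direction of the gain does not depend on them, apart from one degree of freedom. The comparison as planned remains valid under randomization.

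**What to change.** Replace the primary-model sentence in the Analytic plan with wording such as:

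> The primary analysis at 3 and at 12 months regresses log urine cotinine on randomization arm, with log baseline cotinine and presence of other smokers in the home as prespecified covariates and clinic as a random intercept. The arm effect is reported as a ratio of geometric means.

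Using log change as the outcome with the same covariates is equivalent for the arm effect. State the log base. Keep the log change score without baseline adjustment as a sensitivity analysis.

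The cost is wording plus one degree of freedom for log baseline cotinine and one for the stratification factor. Baseline cotinine and the stratification factor are already collected, and the sample size need not change. The wording should be settled before any unblinded outcome data are analysed.

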### Procedures

Prior to initiating participant recruitment, we will conduct a formative analysis of current tobacco intervention practices among professional and paraprofessional staff who work in Philadelphia WIC clinics. This preliminary research will facilitate the translation and implementation of AAR best practices into routine WIC clinic operations and client flow that will minimize both staff and participant burden. We will then provide group training among all staff that highlights the child TSE problem and its consequences, challenges maternal smokers have in quitting smoking, and the pivotal contributing role of community health workers in tobacco control efforts. In addition, WIC nutrition counselors will receive more intensive training in the specific steps to implementing the Ask, Advice, Refer intervention.

After WIC staff refer smoking mothers with exposed children to the trial, trained research assistants will consent eligible participants and collect self-report data at baseline. Data will be collected via structured computer assisted telephone interviewing. This method reduces literacy barriers, minimizes participant burden, and maximizes data reliability. After baseline, participants are randomized to condition. A permuted blocks design was used to randomize participants stratified by clinic site and presence of other smokers in the home living with the participant (yes/no). The randomization schedule was seeded using values obtained from random.org and the project biostatistician provided the allocations to the data collection team in sealed opaque security envelopes. To preserve condition masking, participants will be randomized after baseline data collection and immediately prior to a treatment orientation home visit. During the orientation home visit, participants receive a binder with intervention materials that are relevant to their assigned intervention condition. Research staff also download a mobile app specific to condition on participants’ smartphones and show an app video tutorial, the link to which is left with the participant. The child’s urine cotinine sample is also collected during the home visit.

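### A standard-error test of the mediated effect can cost up to about 22 points of power, and resampling whole clinics inflates false positives if clinics are few

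*Protocol article*

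**What the plan says.** Aim 3 (Aims and hypotheses) states a hypothesis: changes in the mediators by month 3 account for the difference between arms at month 12. The Mediators section says "Four variables will be assessed as potential mediators".

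The Analytic plan then sets out three steps:
- The model: "we will use a structural equation approach with change in cotinine levels and parent quit status as the outcomes".
- A check on each path: "We will ensure that the intervention is associated with the potential mediators (e.g., self-efficacy) and that the mediators are associated with the outcomes".
- The indirect effect itself: "We will also use cluster-adjusted bootstrap standard errors for assessment of the mediated effect".

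The cluster is the clinic. The cotinine model, described earlier in the same section, has "WIC clinic as a random intercept to account for potential clustering within clinic". Allocation, however, is of individual mothers within clinic (Procedures): "A permuted blocks design was used to randomize participants stratified by clinic site and presence of other smokers in the home".

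The article gives no number of clinics, no intraclass correlation (ICC), no path sizes and no power for mediation. Nor does it say what test or interval is built from the bootstrap standard errors.

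**The concern.** The indirect effect is a product, a × b: arm to mediator, times mediator to outcome given arm. Its sampling distribution is skewed unless at least one path is estimated very precisely. A standard error supports a symmetric test, which discards the shape that the bootstrap draws already show. When both paths are modest, that test is too strict.

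The cluster adjustment raises a separate issue. The usual cluster bootstrap draws whole clinics with replacement. With few clinics it understates the standard error and refers the result to a normal distribution that is too narrow. The test is then too lenient.

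At stake is a named hypothesis with about 298 completers: either a real mediator is missed or a false one is claimed, depending on path sizes and clinic numbers that the article does not give.

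**Working it through.** **Inputs from the article.** Power analysis: "we expect to have 298 participants at 12 months (372*80% retention = 298, or 149 per group"). Check: 372 × 0.80 = 297.6, so 298 is reproduced. The only power figure concerns the total effect: "With 149 participants per group, we will have 85.7% power to detect an effect of 0.23 in the log cotinine change scores between randomization arms". No SD is given. With alpha 5% two-sided (assumed), 85.7% needs an SD of about 0.656: 0.23 / (0.656 × √(2/149)) = 0.23 / 0.0760 = 3.03, and Φ(3.03 − 1.96) ≈ 0.857. The implied standardised total effect is 0.23 / 0.656 ≈ 0.35.

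**Inputs assumed.** Path a in SD units between arms, path b standardised, 4 to 30 clinics, ICC 0 to 0.05, continuous outcome.

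**Why the symmetric test is strict (by hand).** Take SE(a) = √(4/298) = 0.116 and SE(b) = 1/√298 = 0.058. To first order the z value for the product is z_a·z_b / √(z_a² + z_b²).
- a = 0.28, b = 0.14: z_a = z_b = 2.42, product z = 1.71. Each path clears 1.96 at its expected value; the product does not.
- a = 0.40, b = 0.20: z_a = z_b = 3.45, product z = 2.44.
- a = 0.78, b = 0.39: z_a = z_b = 6.73, product z = 4.76. The strictness no longer matters.

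**Power by simulation.** N = 298, arms balanced within clinic, whole-clinic bootstrap, 5 to 30 clinics, 400-500 resamples, 1,500 trials per setting. The rows for (0.35, 0.18), (0.30, 0.30), (0.50, 0.20), (0.78, 0.14) and (0.78, 0.39) cover 5 to 20 clinics at ICC 0.02 only.

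| a, b | Estimate/SE test | Percentile interval | Loss (points) |
|---|---|---|---|
| 0.28, 0.14 | 25-44% | 44-59% | 15-22 |
| 0.35, 0.18 | 57-69% | 75-83% | 14-19 |
| 0.40, 0.20 | 70-81% | 86-90% | 9-16 |
| 0.30, 0.30 | 69-77% | 76-83% | 6-9 |
| 0.50, 0.20 | 83-88% | 92-93% | 6-9 |
| 0.78, 0.14 | 65-72% | 69-76% | 3-5 |
| 0.50, 0.30 | 97-98% | 98-99% | 1-2 |
| 0.78, 0.39 | about 100% | 100% | 0 |

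At few clinics, part of the percentile interval's apparent gain is the type I inflation shown below.

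**If the two path checks decide alone.** Power is the product of the two path powers. At (0.28, 0.14) each is Φ(2.42 − 1.96) ≈ 0.676, so 0.676² ≈ 45.7%. At (0.40, 0.20) it is 86.9%. Both are close to the percentile interval, so nothing is lost.

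**Type I error, whole-clinic draws, one path real and the other zero.** The ranges span several independent sets of runs.
- 5 clinics: estimate/SE test about 9-16%; percentile interval about 14-18%, with single settings up to about 20%.
- 10 clinics: about 4-9%; percentile about 9-12%.
- 20 clinics: about 3-7%; percentile about 7-8%.
- Both paths zero: the estimate/SE test rejects in about 3% or less.

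A rough hand check explains the upper ends. With G clinics the bootstrap standard error is too small by about √((G − 1)/G) and has G − 1 degrees of freedom. G = 5: 1.96 × 0.894 = 1.75, and P(|t₄| > 1.75) ≈ 15%. G = 10: 1.96 × 0.949 = 1.86, and P(|t₉| > 1.86) ≈ 10%.

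**The combined fix.** Participants resampled within clinic and arm, clinic in both models, percentile interval; ICC 0.02, 600 trials × 400 resamples, Monte Carlo SE about 1-2 points.
- Type I error with one real path: 5.7-7.0% at both 5 and 10 clinics. All runs of this approach lie at about 4-8%.
- Power at (0.35, 0.20): 80% (5 clinics) and 78% (10), against 62% and 56% for the estimate/SE test on the same stratified draws.

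**The case against.** **The test is inferred.** A reader might take the article to commit to comparing estimate/SE with 1.96. It does not say so, and a condensed article may leave the interval type to the SAP. This stands as a condition on the power result. The article does name the standard error as the quantity for inference, however, and percentile intervals do not use one, so the symmetric test is the natural reading.

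**The path checks may be the real criterion.** If they are, no power is lost. But the text says the bootstrap is used in addition. If both must succeed, power cannot exceed that of the stricter test. If the checks alone decide, the bootstrap sentence has no inferential role.

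**The loss may be small here.** A reader might infer a fixed loss of 12 to 22 points. The article gives no path sizes, and large paths bring the loss to zero. On the other side, the no-loss case (0.78 × 0.39 ≈ 0.30) would need one mediator to carry about 87% of the implied total effect (0.30 / 0.35). An even split of 0.35 over four mediators, with complete mediation and effects of one sign, is about 0.09 each. At indirect effects of that order the loss was about 6-20 points with fairly balanced paths, and less when one path dominates.

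**False positives may not rise.** A reader might also infer that this trial will make false mediation claims. That depends on an unstated number of clinics and on one path being real. The inflation comes from drawing whole clinics, not from using a standard error, so switching to a percentile interval alone would make it worse.

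**The mediator-outcome path is not randomised.** Stratified allocation protects only the arm contrasts. This stands, and is why clinic must stay in the mediator and outcome models.

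**Conclusion.** The point holds conditionally. Read as a symmetric estimate/SE test, the stated method loses between 0 and about 22 points of power against a percentile interval with 149 per arm. The loss is 9 points or more when a is about 0.28-0.40 SD and b about 0.14-0.20, and close to nil when both paths are large. If whole clinics are resampled, type I error with one real path is about 9-16% at 5 clinics and about 4-9% at 10. The two faults pull in opposite directions and have separate causes, so changing only the interval or only the resampling unit leaves one of them in place.

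The figures rest on assumed path sizes, clinic numbers and ICCs, and on a linear model for cotinine change; quit status was not simulated. The point touches Aim 3 only. The primary and secondary comparisons are unaffected, so priority is low to moderate.

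**What to change.** Replace the bootstrap sentence in the Analytic plan with one that makes both changes, for example: *The indirect effect will be tested with a 95% percentile bootstrap confidence interval (for example 5,000 resamples), resampling participants within clinic-by-arm strata, with clinic included in the mediator and outcome models.* It would help to add whether this interval or the two path checks decide mediation.

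The cost is one sentence and re-specified bootstrap draws, with no new data. The approach treats the participating clinics as fixed, so inference is to these clinics and not to a wider population of them. Before it is adopted for quit status, its error rate and power should be checked by simulation for a binary outcome.
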